### 2.6. Interventions

#### Intervention Description

The sample will be randomized systematically and pseudonymized. The 75 subjects will be divided into three intervention groups, and a different intervention will be carried out in each of them:

-Guidance Document Group (*n* = 25): The primary and community care physiotherapist will carry out an individual face-to-face consultation at the Primary Care Center with the person participating in the study, where they will deliver a guide document for the management of the pathology, as well as guidelines for the promotion and prevention of important health issues after a stroke. The document is the “Guide aimed at people affected by cerebral vascular disease and their families and caregivers” created by the Department of Health of the Generalitat de Catalunya, together with the Stroke Foundation in 2022. This group is the control, since the intervention is the one that most resembles the intervention that is currently being carried out in Catalonia from the Primary Care Centers for Stroke in the chronic phase.

No additional therapeutic contacts are scheduled after this initial session, and no monitoring is performed, as this reflects current standard practice in Catalonia.

No adherence tracking applies in this group, as no structured exercise program is prescribed.

-Therapeutic Exercises Document Group (*n* = 25): The physiotherapist will carry out an individual face-to-face consultation at the Primary Care Center with the person participating in the study. The document “Home-Based Therapeutic Exercise Program” will be explained and delivered, and contains an exercise program to be carried out during the next 10 weeks, with a frequency of 3 times a week. The explanatory document consists of 3 exercise tables for each week of intervention (30 sessions) [48,49,50,51,52]. In addition to the corresponding description of each exercise for the correct performance, it will also specify the dosage, both in repetitions, as well as in series and load to be performed. It will also contain a checklist template for tracking completed activities. Strength exercises will be performed for the different muscle groups of the lower extremity and upper extremity, and trunk. Also, stretching exercises for the most relevant flexor muscles of the lower extremity and upper extremity and trunk will be undertaken. In addition, stretching exercises will be included for the most relevant flexor muscles of these regions. In addition, exercises wil be added for the efficiency of standing walking, such as the previous step. And, finally, mobility exercises and global balance will be included.

Although the exercise dose is identical to that of the telerehabilitation group (30 sessions over 10 weeks), participants in this group will also receive structured follow-up contacts. A brief telephone call (approximately 10–15 min) will be scheduled every two weeks (five contacts in total) to review adherence, address questions regarding the exercises and, when necessary, adjust the dosage or difficulty according to predefined criteria. Any additional clarification requested by participants will follow the usual communication channels of the primary care center, but no structured monitoring is performed.

Participants in this group will self-record adherence using the checklist provided within the exercise program.

-Telerehabilitation Group (*n* = 25): The physiotherapist will carry out an individual face-to-face consultation at the Primary Care Center with the person participating in the study, where the intervention of an individualized program of therapeutic exercises will be explained through a Telerehabilitation platform (Physitrack) for the following 10 weeks, with a frequency of 3 times a week (30 sessions). In addition, participants will be given an explanatory document called “Guide for the use of the Physitrack Telerehabilitation Platform” that contains the necessary information for the correct access and use of Physitrack. Likewise, the consultation will include a brief overview of the platform’s operation and a practical demonstration. The therapeutic exercise program will follow the same standardized structure and dosage as that of the Therapeutic Exercises Document Intervention Group (same exercices, number of sessions, sets, repetitions, intensity, and progression criteria). Participants in this group will receive structured follow-up every two weeks (five contacts in total), delivered through the telerehabilitation platform. These remote contacts (approximately 10–15 min each) will allow the physiotherapist to review adherence, address questions, and adjust the exercise program according to each patient’s progression. Participants will also be able to communicate directly with the physiotherapist through the platform.

In both the Therapeutic Exercises Document Group and the Telerehabilitation Group, the initial therapeutic exercise program is standardized. Each session includes approximately 8–10 exercises targeting the lower limbs, upper limbs, and trunk, combining strengthening, stretching, mobility, and balance tasks. Unless otherwise indicated, exercises are prescribed in 2–3 sets of 10–15 repetitions, at a moderate intensity guided by perceived exertion (11–13 on the Borg scale), with 1–2 min of rest between sets. Progression is applied every two weeks according to predefined criteria (e.g., increasing repetitions, sets, or load, or introducing a more challenging variation) when the patient is able to complete the exercises with good technique and without excessive fatigue or pain. A detailed description of the exercises and progression criteria is provided in Supplementary Table S1.

To ensure consistency across intervention groups, participants will be instructed to maintain only their usual daily physical activity during the study period. No additional structured physiotherapy, private rehabilitation, or external therapeutic exercise programs will be permitted, as these could influence the outcomes of the assigned intervention. Compliance with these instructions will be monitored through a weekly activity log completed by participants and reviewed by the physiotherapists, allowing the identification of any concomitant activities.

In addition, with the aim of analyzing the actual dose of treatment received, adherence will be assessed in all intervention groups based on the proportion of prescribed sessions completed, the weekly frequency achieved, and the duration of each session. These parameters will be systematically recorded to determine the effective exercise dose performed by each participant and to explore its potential influence on functional outcomes.

Finally, once the intervention period and the two-month follow-up evaluation (T2) have been completed, if the Telerehabilitation Group demonstrates superior results compared with the other two groups, participants from those groups will be offered the opportunity to receive an individualized therapeutic exercise program through the Physitrack platform. This measure ensures that all participants may benefit from the most effective therapeutic option, thereby upholding the ethical principles of equity and beneficence in research.

### 2.7. Safety Monitoring and Adverse Events

To ensure participant safety throughout the intervention period, all adverse events (AEs) occurring during the study will be systematically monitored, documented, and reported in accordance with institutional guidelines and research ethics standards.

Expected adverse events in the context of a therapeutic exercise program for individuals with chronic stroke may include mild musculoskeletal pain, transient fatigue exacerbation, dizziness, or accidental falls. Although these events are considered low risk, any occurrence will be recorded in detail and reviewed by the study physiotherapists.

An adverse event will be documented when a participant reports new symptoms, an exacerbation of pre-existing symptoms, or any physical incident occurring during or after an exercise session. The participant’s designated physiotherapist will record the event in the document specifically created for this purpose within the study’s secure system, including the date, description, severity, actions taken, and whether the participant required additional medical evaluation. Serious adverse events (SAEs), such as injuries requiring medical attention or hospital admission or any incident that compromises participant safety, will be reported immediately to the principal investigator.

All SAEs, as well as any adverse events judged to be related to the intervention, will be reported to the Research Ethics Committee (CEI) in accordance with institutional and regulatory requirements. The CEI will be informed within the timelines established by the institution’s protocols. Participants experiencing an adverse event will be assessed and, if necessary, may be temporarily or permanently withdrawn from the intervention to ensure their safety.

Regular safety monitoring will be carried out throughout the study by the principal investigator, who will oversee adherence to reporting procedures and ensure that all safety-related information is appropriately reviewed and managed.

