## 4. Conclusions

Chronic stroke patients with a stable clinical condition but residual functional disability require a continuous, individualized rehabilitation approach adapted to the different stages of their lives. Rehabilitation care should not only focus on initial recovery but also on preventing progressive functional decline and secondary conditions associated with physical inactivity and disability. In this context, therapeutic exercise is established as a fundamental tool for maintaining long-term functional autonomy and quality of life.

The results of this study may provide relevant evidence on the effectiveness of telerehabilitation as a complementary or alternative therapeutic modality to traditional in-person care. If proven effective in improving key functional variables—such as the ability to perform activities of daily living, muscle strength, balance, and perceived quality of life—this strategy could be integrated into Primary Care services. This would allow for expanded access to rehabilitation programs, particularly in rural or resource-limited areas, thereby promoting equitable, sustainable, and patient-centered care.

However, potential barriers to implementation in Primary Care must be acknowledged. These include the need for adequate technological infrastructure, sufficient digital literacy and training for both clinicians and patients, and the variability in resource availability across regions, particularly in rural settings. Additionally, reimbursement policies and organizational models may need adaptation to incorporate remote rehabilitation within existing service frameworks. Despite these challenges, the findings of this study may help guide future implementation strategies by identifying the conditions under which telerehabilitation can be safely, feasibly, and effectively deployed in real-world Primary Care environments.

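### The adverse-event routes described rest largely on exercise sessions and fortnightly contacts that the control arm lacks, so events are likely to be captured less completely there

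*Protocol article*

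**What the plan says.** Section 2.7 sets the standard: "all adverse events (AEs) occurring during the study will be systematically monitored". The same sentence opens with a narrower period: "To ensure participant safety throughout the intervention period". An event is documented when a participant reports "new symptoms, an exacerbation of pre-existing symptoms, or any physical incident occurring during or after an exercise session". As to who writes it down, "The participant’s designated physiotherapist will record the event in the document specifically created for this purpose". Falls appear in the list of expected events, which is framed around taking part in an exercise programme.

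Section 2.6 (Intervention Description) says of the control arm: "No additional therapeutic contacts are scheduled after this initial session, and no monitoring is performed". The Limitations section repeats that control receives one session without further monitoring. Section 2.6 also gives each exercise arm a physiotherapist contact every two weeks, five in all: by telephone for the document group, and through the platform for the telerehabilitation group, which can also message the physiotherapist directly.

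Section 2.2 has incidents recorded at each session of the ten-week intervention. It describes T1 and T2 as visits for efficacy data, held with the evaluating physiotherapist. Sections 2.4 and 2.6 give all participants a weekly activity log to detect concomitant therapy; Section 2.4 has it verified at follow-up contacts.

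**The concern.** A count of adverse events by arm can be read as a comparison only if the same events are looked for in the same way in every arm. Here the procedure rests on a participant telling a physiotherapist, and the scheduled occasions for doing so fall mainly in the two exercise arms. Part of the definition also refers to something that control participants do not do.

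Three things are at stake.

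- Equal true event rates could appear as an excess in the exercise arms.
- A fall or injury in a control participant may surface only if that person volunteers it, although Section 2.7 wants serious events reported to the principal investigator immediately.
- The Conclusions express the hope of "identifying the conditions under which telerehabilitation can be safely, feasibly, and effectively deployed", and readers will look to the safety data for that.

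Events that were never asked about cannot be recovered by a later analysis plan.

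**Working it through.** The plan states no figure on this point, so there is none to reproduce. The check sets each route described in the article against the three arms.

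1. **Physical incidents (Section 2.7).** The wording is "any physical incident occurring during or after an exercise session". Both exercise arms have 30 prescribed sessions (3 per week × 10 weeks); control has 0. A control participant's fall at home does not clearly meet this wording.
2. **New or worsened symptoms (Section 2.7).** These can be read as reportable in any arm, because the session condition clearly governs only the physical incidents.
3. **Incidents recorded per session (Section 2.2).** Available in the exercise arms only.
4. **Scheduled physiotherapist contacts after the first consultation and before T1 (Section 2.6).** Control 0, document group 5, telerehabilitation group 5.
5. **T1 and T2 (Section 2.2).** All arms attend both. Scheduled occasions after the first consultation are then 0 + 2 = 2 in control and 5 + 2 = 7 in each exercise arm. The article does not say that adverse events are asked about at these visits.
6. **Weekly log (Sections 2.4 and 2.6).** All arms, but its stated purpose is concomitant activity. Section 2.4 ties its verification to follow-up contacts, which control does not have before T1.
7. **Between T1 and T2.** Scheduled contacts are 0 in every arm, so any gap there is shared.

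Routes 1, 3 and 4 operate only in the exercise arms. Route 2 is open to all, but it depends on the participant coming forward. Routes 5 and 6 reach all arms but are not described as collecting adverse events.

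*Illustration only; none of these inputs is in the documents.* Let the true risk of at least one event be 30% in every arm, with 25 participants per arm and 90% capture in an exercise arm. The expected number recorded is 25 × risk × capture, and the recorded risk ratio is the ratio of the two capture probabilities.

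- Exercise arm: 25 × 0.30 × 0.90 = 6.75.
- Control at 90% capture: 6.75; ratio 1.00.
- Control at 70% capture: 5.25; ratio 0.90/0.70 = 1.29.
- Control at 50% capture: 3.75; ratio 0.90/0.50 = 1.80.
- Control at 30% capture: 2.25; ratio 0.90/0.30 = 3.00.

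These ratios only restate the assumed capture rates. They show the direction of the bias and how it scales, and are not an estimate for this trial.

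**The case against.** The strongest reply is that monitoring in Section 2.6 means therapeutic follow-up, not safety surveillance. The sentence sits in the description of the intervention, next to a remark on adherence tracking. The article also says that the document group has no structured monitoring, in the same paragraph that schedules its five calls. On that reading, Sections 2.6 and 2.7 need not contradict each other. This is a fair reading, and it is why the point does not rest on that one word. It does not supply a route by which control events are sought.

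Several stronger inferences are tempting, and the documents do not support them.

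- **Control has no contact at all.** It attends T1 and T2 and keeps the weekly log.
- **All adverse events are tied to exercise sessions.** Only physical incidents clearly are, and the rule for serious events carries no session condition.
- **Only control can lose events.** No arm has a scheduled contact between T1 and T2.
- **A fall-related outcome is biased.** Fall risk is measured by the Timed Up and Go, performed with blinded assessors in all arms. Pain and fatigue are likewise measured with the same scales in all arms. Only falls and symptoms recorded as adverse events are exposed.
- **A planned analysis is invalid.** Adverse events are not listed as outcomes, and Section 2.8 plans no comparison of them. The remark on safe deployment is conditional and concerns telerehabilitation, whose nearest comparator, the document group, has the same number of contacts.

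It is also true that the fortnightly contacts are described as reviewing adherence, answering questions and adjusting the programme, so they are opportunities to report rather than stated safety enquiries. Finally, an article may leave forms and recall windows to the full protocol. That covers missing detail. It does not cover a session-linked definition and an uneven set of routes that the article itself states.

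**Conclusion.** The concern holds in a limited form. The article promises systematic monitoring of all adverse events, but the routes it describes favour the exercise arms, so capture in control is likely to be less complete, above all for falls and injuries that have nothing to do with exercise. The likely direction is to make the exercise arms look less safe than control.

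The firm quantity is the schedule: 0, 5 and 5 contacts before T1. The size of any bias cannot be derived from the documents. The conclusion assumes that more scheduled contact leads to more reporting, and that no unshown procedure asks control participants about events. It does not touch the primary outcome or any listed secondary outcome. This should be changed, because the repair is cheap and lost events cannot be recovered afterwards.

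**What to change.** - Reconcile Sections 2.6 and 2.7: state that the absence of monitoring in control refers to therapeutic follow-up (if that is meant), and that safety surveillance covers all three arms. Settle whether it runs for the intervention period or to T2.
- Define an adverse event identically in all arms from T0 to T2: any new or worsened symptom, fall or injury, whether or not it is linked to a session.
- Collect it by one common route: a short adverse-event and falls item on the weekly log that participants already keep, and one standard question at T1 and T2. Ask that question so that the answer does not reveal the arm to the blinded assessor, for example on a self-completed form.
- Report events from this common route by arm, separately from events that came up only in the fortnightly contacts.
- If this is not done, state that adverse-event rates will not be compared between control and the exercise arms.

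The cost is a few lines on existing forms, slightly more recording, and more control-arm events to process, most of them probably mild. Control gains no therapeutic contact, so the contrast under test stays as it is.

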### 2.8. Statistical Analysis

The statistical analysis will be performed with the IBM SPSS v.26.0 software. Descriptive statistics will be calculated for all variables. To check the normal distribution of the variables, the Kolmogorov–Smirnov test with the Lilliefors correction will be used. For the comparison of the groups, a mixed 3 × 3 ANOVA will be carried out with interaction time (three measurement time points) and group (three intervention groups). The assumption of sphericity will be checked by means of the Mauchly test; if it is not met, the Greenhouse–Geisser correction will be used for interpretation.

The primary outcome and the Key Secondary Outcomes (motor function, muscle tone, muscle strength, balance, and quality of life) will be analyzed following this main model, given their clinical relevance. Additional Secondary Outcomes (gait performance, perceived pain, fatigue, fall risk, and subjective perceived change) will be analyzed using the same statistical approach but interpreted with greater caution due to their supplementary nature.

When a statistically significant effect is observed, the post hoc test will be performed using the Bonferroni correction to adjust for multiple comparisons. This correction will be applied systematically to all post hoc analyses to address the multiplicity of secondary outcomes.

For qualitative variables, the Chi-square test or Fisher’s Exact statistic will be used. The effect size will be calculated using Cohen’s d. Cohen’s coefficients [53] are interpreted as follows: large effect sizes, d > 0.8; moderate effect sizes, d = 0.5–0.79; and small, d = 0.2–0.49. The significance level was established at *p* < 0.05 with a 95% confidence interval. Missing data will be handled using Little’s MCAR test and multiple imputation (MICE) performed separately for each intervention group using the SPSS multiple imputation module. The analysis will be undertaken on an “intent-to-treat” basis.

Adherence outcomes (percentage of sessions completed, weekly frequency, and session duration) will be analyzed descriptively and compared between groups. If appropriate, exploratory analyses (e.g., correlation or regression models) will be conducted to examine the potential mediating or moderating role of adherence in relation to functional outcomes.

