## Abstract

**Background**: Stroke is the leading cause of physical disability in adults in Catalonia. Despite this, there is a lack of evidence of physiotherapy interventions on functional capacity during the chronic phase of the pathology. This multicenter clinical trial will be conducted with a sample size of 75 participants. **Objectives**: The objective of the study is to evaluate the effectiveness of a therapeutic exercise program in physiotherapy using telerehabilitation to optimize functional recovery and quality of life in people with chronic stroke, and to determine its impact on adherence to the exercise program. **Methods**: This is a multicenter randomized controlled trial. Three parallel groups will be compared, and two will undergo the same type of therapy. A control group (CG) will perform conventional intervention in primary care. There will be two experimental groups; (EG1) will perform document-guided therapeutic exercises at home and (EG2) will perform therapeutic exercises at home guided by a telerehabilitation program. The outcomes to be measured are degree of independence of a person in their activities of daily living, assessed by the Barthel Index, motor function, muscle tone of the affected limbs, muscle strength of the affected limbs, balance, gait efficiency, perception of musculoskeletal pain, perception of fatigue, risk of falls, perception of quality of life, and the perception of perceived subjective change after treatment. These outcomes will be evaluated at baseline (T0), at ten weeks (T1) (end of the intervention), and at 18 weeks (T2). The study duration per patient will be 18 weeks (a ten-week intervention, followed by an eight-week intervention follow-up). The analysis will be performed using a mixed linear model (ANOVA 3X3) and significance level *p* < 0.05.

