After group allocation and before starting treatment (T0), pre-intervention tests will be conducted to assess the baseline values of the primary and secondary outcome measures. A maximum of one week after completion of the intervention (T1), data will be collected for all efficacy outcomes (see Section 2.5). The same data will be collected two months after the end of the intervention (T2) (Figure 1). During the ten weeks of intervention, data will be collected in each session regarding adherence to the intervention (number of sessions and duration), intensity, exercises performed by each patient, and any incidents. All visits and efficacy evaluations will be conducted at the patient’s reference primary care center with the corresponding evaluating physiotherapist.

The study uses a single-blind design due to the nature of the interventions; therapists and participants cannot be blinded to treatment allocation. To avoid detection bias, efficacy outcomes will be assessed by an independent, blinded evaluator. Each center has a trained physiotherapist assessor, supervised by the principal investigator. The training information is available online and in paper format. Additionally, all statistical analyses will be conducted by researchers blinded to group allocation.

All data will be recorded in an online document shared by all the evaluators of the research team. A form created in a spreadsheet will be used. All researchers are trained in the use of the scales and the document, and they have a help guide, as well as a consultation service directly with the principal investigator of the study who is responsible for the logistics of the study. Access to the study registration document is restricted to authorized study personnel via password.

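### The primary ANOVA treats pre-treatment Barthel as an outcome level, does not say which significant effect opens the post hoc tests, and names no deciding contrast or visit

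*Protocol article*

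**What the plan says.** Section 2.8 of the protocol article states that, to compare the groups, "a mixed 3 × 3 ANOVA will be carried out with interaction time (three measurement time points) and group (three intervention groups"). The primary outcome and the key secondary outcomes "will be analyzed following this main model, given their clinical relevance".

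The Abstract gives the three visits: "These outcomes will be evaluated at baseline (T0), at ten weeks (T1) (end of the intervention), and at 18 weeks (T2"). Section 2.2 places T0 before treatment: "After group allocation and before starting treatment (T0), pre-intervention tests will be conducted to assess the baseline values". Pre-treatment Barthel is therefore one of the three outcome levels. No baseline covariate is mentioned.

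The step from the ANOVA to group differences is: "When a statistically significant effect is observed, the post hoc test will be performed using the Bonferroni correction to adjust for multiple comparisons". The sentence does not say whether the effect is group, time or their interaction.

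Section 2.5 names the Barthel Index as primary without a visit. The objective at the end of the Introduction concerns exercise delivered by telerehabilitation; the comparison with paper delivery is stated there for adherence only. Section 2.6 makes a later offer of the platform depend on the telerehabilitation group doing better than both other groups, without a test or visit.

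**The concern.** There are three linked weaknesses.

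- **Baseline as outcome.** Treatment cannot affect T0. Averaging over three visits shrinks any group difference, and comparing groups visit by visit ignores a baseline value that every participant will already have supplied.
- **Open gate.** A time effect says nothing about differences between arms. If it can open the post hoc tests, the ANOVA gives almost no protection against a false group difference whenever all arms improve.
- **No deciding comparison.** An omnibus result can be significant because both exercise arms beat control equally. That would not show that the telerehabilitation format adds anything, yet the superiority wording in Section 2.6 needs exactly that.

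At stake are power in a trial of 25 per arm, control of false group claims, and freedom to choose effect, contrast and visit after the data are seen.

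**Working it through.** **Inputs from the protocol article.** Three arms of 25; three visits; f = 0.32; α = 0.05; power 0.80; dropout 10%; expected difference 8–10 Barthel points (Sections 2.1 and 2.3). **Assumed, because not stated:** the correlation r between visits (0.5–0.8), equal correlations, normal data with SD 1, the same effect at T1 and T2, and Bonferroni over three pairs per visit. Dropout leaves 25 × 0.9 = 22.5 per arm, so 22 or 23 is used.

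**1. The plan's sample size.** For the group effect in a repeated-measures ANOVA, λ = f²·N·m / (1 + (m − 1)r). With f² = 0.1024, N = 66, m = 3 and r = 0.5, λ = 0.1024 × 66 × 3 / 2 = 10.14 on 2 and 63 df, which gives power 0.80. Then 66 / 0.9 = 73.3, so 74, or 75 in equal arms. The stated 75 reproduces.

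**2. Dilution.** That calculation takes f = 0.32 as the effect averaged over all three visits. If it describes the difference after treatment, the three-visit mean difference is (0 + d + d)/3 = 2d/3. Then f falls to 0.213 and λ to 10.14 × 4/9 = 4.51, and the group-effect power falls from 0.80 to 0.44.

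**3. Effect size per pair.** If one arm differs, d = 3f/√2 = 0.68. If the arms are equally spaced, the extreme pair differs by d = f√6 = 0.78. With 8–10 points this implies a Barthel SD of about 10 (8/0.78) to 15 (10/0.68).

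**4. The interaction F.** Power with 22 per arm, only the telerehabilitation arm differing, by 0.68 SD:

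| Test | r = 0.5 | r = 0.7 | r = 0.8 |
|---|---|---|---|
| Group × time interaction | 0.65 | 0.88 | 0.98 |
| Three-group ANCOVA at T1 | 0.74 | 0.89 | 0.97 |
| Three-group ANCOVA, mean of T1 and T2 | 0.90 | 0.97 | 1.00 |

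Against ANCOVA at one visit the interaction loses something at r = 0.5 and almost nothing from 0.7 upwards.

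**5. The pairwise step.** Telerehabilitation versus control at T1, 23 per arm, two-sided 0.05/3 (critical t about 2.46). The unadjusted standard error is √(2/23) = 0.295. Baseline adjustment multiplies the variance by 1 − r², which is 0.75 at r = 0.5 and 0.51 at r = 0.7, so the standard errors are 0.255 and 0.211.

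| | d/SE at d = 0.68; 0.78 | Power |
|---|---|---|
| Unadjusted, before any gate | 2.31; 2.65 | 0.44; 0.58 |
| Baseline-adjusted, r = 0.5 | 2.66; 3.05 | 0.58; 0.72 |
| Baseline-adjusted, r = 0.7 | 3.23; 3.70 | 0.78; 0.89 |

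Simulation of the whole planned route gives 33–56% if the interaction must be significant first and 43–57% if any effect will do. With baseline adjustment at the same Bonferroni level it gives 58–89%.

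**6. The gate.** Simulation with no group effect, a common gain of 0.4 SD at T1 and T2, 23 per arm, r = 0.5–0.7:

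| Effect that opens post hoc tests | How often it opens | False group pair at T1 or T2 |
|---|---|---|
| Any of the three | about 93–99% | about 7–8% |
| Interaction only | 5% (nominal) | about 1% |

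**7. What a significant F means.** If both exercise arms beat control equally by 0.68–0.78 SD, the interaction is significant in 67–96% of simulated trials, although telerehabilitation adds nothing to paper delivery.

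**The case against.** The strongest reply is that Section 2.8 introduces the ANOVA for comparing groups and names only the interaction, so the later sentence on a significant effect may mean that one. On that reading the F test has 5% error and false pairs are rare. This is fair. A reader might infer that the plan certainly lets the time effect open the tests; the text leaves this unsettled, and the 7–8% applies only to the literal reading. What stands is that the sentence does not say.

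A group-by-time ANOVA with baseline as a level is also a valid analysis, and step 4 shows that its interaction test is not weak at high correlations. A reader might infer that the primary test is invalid or badly underpowered. The documents do not support that; the clear loss is in the group main effect and the pairwise comparisons.

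The size of that loss is easily overstated. Setting the planned Bonferroni route beside one adjusted contrast at 0.05 mixes baseline handling with multiplicity. Pairing the interaction gate's lower power with the any-effect gate's higher error charges the plan with two readings at once. At r = 0.5, with any effect as gate and success at either T1 or T2 counted, the planned route reaches about 60–62% (d = 0.68) and 74–76% (d = 0.78), against 58% and 71% for adjusted T1 alone. That reply gives the plan two visits and the alternative one. At r = 0.7 the adjusted analysis is ahead even so (77–88% against 57–71%).

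Two further inferences should be left aside. One is that "multiple imputation (MICE) performed separately for each intervention group using the SPSS multiple imputation module" cannot feed the planned ANOVA: the article does not say how imputed results will be combined, and nothing in it rules out a workable method. The other is that the Abstract's "The analysis will be performed using a mixed linear model (ANOVA 3X3") names a rival model: it equates the two terms.

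Finally, a separate analysis plan may name the contrast and visit. That is possible, but the article itself fixes the model and the gate, and as written they do not single out the telerehabilitation question.

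**Conclusion.** The point holds in limited form. The primary model spends one of three outcome levels on a pre-treatment value, the rule for opening post hoc tests is ambiguous, and no contrast or visit decides the trial.

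At equal Bonferroni level, baseline adjustment raises the chance of showing telerehabilitation versus control at T1 from about 33–57% to 58–89%. The literal gate gives false group pairs in about 7–8% of trials when all arms improve, against about 1% under an interaction-only gate. These figures rest on r = 0.5–0.7, 23 per arm, d = 0.68–0.78 and normal data; the documents state neither the correlation nor the Barthel SD. The direction of the precision gain does not depend on the exact r, but its size does.

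A significant telerehabilitation-versus-control result would not by itself show that the format adds benefit over paper, because it also appears when both exercise arms are equally better than control.

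**What to change.** Rewrite the primary analysis in Section 2.8, before group allocation is unblinded:

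- Fit a linear mixed model in the same software to Barthel at T1 and T2, with group, visit, group × visit, baseline Barthel and baseline × visit.
- State one primary visit, for example T1, the end of the intervention.
- Base group claims only on named baseline-adjusted contrasts, never on the time effect.
- Name telerehabilitation versus control and telerehabilitation versus paper exercise, with a stated multiplicity rule such as a fixed sequence or Bonferroni.
- Require both contrasts for the claim in Section 2.6 that telerehabilitation is superior to the other two groups.

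The order of the contrasts and the choice of visit are the sponsor's to make. The change needs no new data, participants or software. The small cost is that the omnibus F is no longer the headline result.
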